### **8.6.3. Change of Treatment**

For many reasons patients operations are cancelled, or patients withdraw themselves from the surgical waiting list. If patients have been randomised into the study and then do not go on to have surgery; reasons for cancellation/withdrawal will be recorded, if available and patients, if willing, will be followed up accordingly.

In the event of discontinuation or withdrawal from the trial the reason will be recorded on the Case Report Form (CRF). Analysis will be performed on an intention-to-treat basis.

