## 6.2 Analysis Methods

### Primary outcomes

### Primary analysis

QoR-40 scores at 72 hours post-surgery will be summarised by treatment group using unadjusted means and associated SDs (see Table 10). QoR-40 scores from baseline to 12 months post-randomisation will also be summarised by treatment group using a boxplot.

A mixed effects linear regression model adjusting for type of surgery, baseline QoR-40 scores, age, and gender as fixed effects and recruitment centre as a random effect will be used compare QoR-40 scores at 72 hours post-surgery. The adjusted mean difference between the arms, associated 97.5% confidence interval and associated p-value will be reported (Table 10). The assumption of approximate normality of the residuals will be assessed graphically.

Pain scores from baseline to 12 months post-randomisation will be summarised by treatment group using a boxplot.

A summary statistics approach will be used to calculate the area under the curve (AUC) of cumulative daily pain scores from 6 to 72 hours post-surgery [24]. Specifically, parameters from a repeated measures mixed effects linear regression model will be used to calculate the pain AUC for each treatment group. The model will include repeated measures of the pain scores (level 1) nested within participants (level 2) and adjusted for recruitment centre as a random effect (level 3). Time will be treated as categorical and a treatment by time interaction will be included. The model will be adjusted for type of surgery, baseline pain score, age, gender, and the use of pre-operative opiate pain medication as fixed effects. The AUC for each treatment group and associated SD will be calculated following the formula lay out by Bell et al. [24] and using the lincom command in Stata. Time will be treated linearly and AUCs will be calculated for the median values of continuous covariates and most common value of categorical covariates. These results will be presented as shown in Table 10. Similar methods will be used to calculate the difference between the two groups which will be compared using a t-test. The adjusted difference (97.5% CI) and associated p-value will be presented (Table 10). The assumption of approximate normality of the residuals of the mixed effects model will be assessed graphically.

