### Secondary analysis

Repeated measures of each of the primary outcomes (at 6, 24, 48, 72 hours, 6 weeks, 6 months and 1 year) will be modelled using multi-level mixed-effects linear regression models. The assumption of approximate normality of the residuals will be assessed graphically. These models will use repeated measures (level 1) nested within participants (level 2) and will include a random effect to account for heterogeneity in response due to recruitment centre (level 3). The models will also include fixed effects for type of surgery (TKR versus UKR), baseline values, age, gender and, in the case of the pain scores, use of pre-operative opiate pain medication. Time will be treated as categorical and interactions between treatment and time will be included in the model to allow for treatment effects to vary over the follow-up. The adjusted difference between treatment groups (and associated 97.5% confidence interval) will be reported (see Table 11). This analysis will be conducted for the ITT population (see Section 4.2).

If, in either case, approximate normality of the residuals is not appropriate, the first approach will be to consider a transformation of the data. If approximate normality cannot be achieved by transformation, the data will be analysed separately at each time point using a non-parametric equivalent with no adjustment. Medians and inter-quartile ranges will be reported for each treatment group.

In addition, a summary measures approach to cumulative pain will also be used as a supporting analysis for this outcome. For each participant, cumulative pain score from 6 to 72 hours post-surgery will be calculated as the area under the curve. Participants with missing pain scores at either 6 or 72 hours will be excluded from this analysis. The potential impact of missing data will be investigated separately. Pain score AUCs will be summarised by treatment group using unadjusted means and associated SDs (Table 11). A multivariate linear regression will be used to compare the AUCs between the treatment groups, adjusted as described previously. The adjusted difference (97.5% CI) and associated p-value will be presented (Table 11).

**Table 11:** Secondary analysis of primary outcomes (ITT population)

|          |                      | Intervention |           | Control |           | Adjusted diff | p-value |
|----------|----------------------|--------------|-----------|---------|-----------|---------------|---------|

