| Fitness for discharge | Day 0 |  | X            | X | X       | X | X (X,X)             | X (X,X) |
|                       | Day 1 |  | X            | X | X       | X | X (X,X)             | X (X,X) |
|                       | Day 2 |  | X            | X | X       | X | X (X,X)             | X (X,X) |

|                      |                     |   |   |   |   |         |         |
|----------------------|---------------------|---|---|---|---|---------|---------|
|                      | Day 3        | X | X | X | X | X (X,X) | X (X,X) |
| Complications | N overall    | X | - | X | - | -       | -       |
|                      | Participants | X | X | X | X | X (X,X) | X (X,X) |

**Table 14:** Comparison of fitness for discharge and actual discharge status

|              |                              | Intervention (n, %) |                       | Control (n, %) |                       |
|--------------|------------------------------|----------------------------|-----------------------|-----------------------|-----------------------|
|              |                              | Discharged          | Not discharged | Discharged     | Not discharged |
| Day 0 | Fit for discharge     | X (X)                      | X (X)                 | X (X)                 | X (X)                 |
|              | Not fit for discharge | X (X)                      | X (X)                 | X (X)                 | X (X)                 |
| Day 1 | Fit for discharge     | X (X)                      | X (X)                 | X (X)                 | X (X)                 |
|              | Not fit for discharge | X (X)                      | X (X)                 | X (X)                 | X (X)                 |
| Day 2 | Fit for discharge     | X (X)                      | X (X)                 | X (X)                 | X (X)                 |
|              | Not fit for discharge | X (X)                      | X (X)                 | X (X)                 | X (X)                 |
| Day 3 | Fit for discharge     | X (X)                      | X (X)                 | X (X)                 | X (X)                 |
|              | Not fit for discharge | X (X)                      | X (X)                 | X (X)                 | X (X)                 |

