### 6.3 Missing Data

For each of the co-primary and secondary outcomes, the number and percentages of individuals in the missing category will be presented by treatment group, as well as reasons for missingness if known. The pattern of missingness will also be explored.

Based on the available data, the possibility of informative missingness, or data being missing not at random cannot be ruled out. Therefore, sensitivity analysis for missing data will examine the effect on the trial conclusions assuming that data are missing not at random, that is that those with missing data may have different outcomes than those with observed follow-up data.

Specifically, the potential effect of informatively missing data on the QoR-40 will be assessed using Stata's *rctmiss* command. Hereby outcomes for all of those with missing outcome data, and separately for those with missing outcome data in the treatment group, will be assumed to be, on average, up to 5 points worse than under a missing at random assumption. 5 points on the QoR-40 were chosen as this was the target difference used in the sample size calculation.

For the cumulative pain AUC analysis, the summary measures approach will be repeated based on the following imputations:

- Missing data at 6, 24, 48 and 72 hours for those in the whole sample known to have been discharged from hospital at the relevant timepoint will be replaced by a pain score of 3, i.e. the cut-off for participants being deemed fit for discharge.
- Missing pain scores at 6, 24, 48 and 72 hours for those in the whole sample not known to have been discharged from hospital by the relevant time point will be imputed with the worst pain score observed across both trial groups at this time point.

The main purpose of the sensitivity analysis for missing data is to examine if the change in the assumptions made about missing data change the trial conclusions.

For individual missing items on a questionnaire, the imputation rules will be as follows:

- QoR-40: if 3 or fewer answers are missing median imputation based on the other questions in the same domain will be used. If more than 3 answers are missing, the total score will be treated as missing.
- OKS: mean imputation based on the response to all other questions will be used for missing items on the OKS if 2 or fewer answers are missing. If more than 2 answers are missing, the total score will be treated as missing.

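### The only missing-not-at-random check for co-primary pain sets missing scores by discharge status, so a difference in discharge between arms can look like a difference in pain

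*Combined protocol and SAP*

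**What the plan says.** SAP 6.3 accepts that informative missingness cannot be excluded. For the pain AUC, "the summary measures approach will be repeated based on the following imputations":

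- at 6, 24, 48 or 72 hours, the missing score of a patient known to have left hospital "will be replaced by a pain score of 3, i.e. the cut-off for participants being deemed fit for discharge";
- the missing score of a patient not known to have left "will be imputed with the worst pain score observed across both trial groups at this time point".

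This repeats a secondary analysis. SAP 6.2 (Secondary analysis) says that "a summary measures approach to cumulative pain will also be used as a supporting analysis for this outcome". The primary pain result comes from a different method: "parameters from a repeated measures mixed effects linear regression model will be used to calculate the pain AUC for each treatment group" (SAP 6.2, Primary analysis).

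For QoR-40, SAP 6.3 takes another route. Missing outcomes are assumed to be up to 5 points worse than under missing at random, first for everyone with missing data and then for the treatment group only.

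Three other places matter:

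- Protocol 6.3 has patients who go home before 72 hours telephoned daily for pain and QoR-40, with a further call if they are not reached.
- SAP 4.2 defines the intention-to-treat population as everyone randomised.
- Protocol 8.6.3 provides for the case "If patients have been randomised into the study and then do not go on to have surgery", with follow-up if the patient is willing.

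**The concern.** Discharge is a post-randomisation event. The protocol's background section hopes the drug will allow it earlier, and fitness for discharge is a secondary outcome. Two patients whose pain is equally unknown can be given values up to 7 points apart because one has gone home. If one arm goes home sooner, its missing scores are filled with lower values. A check meant to stress the result can then favour that arm.

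The value 3 is also weakly grounded. It is the upper limit of one of four discharge criteria, applied at the time of assessment. It does not measure pain on later evenings at home. SAP Table 14 allows for patients discharged while in the "Not fit for discharge" row, although an empty table shell says nothing about how many there will be.

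Finally, SAP 6.3 does not say what happens to randomised patients who have no operation. Taken literally, they are not known to have been discharged, so they would receive the worst observed post-operative score at all four times.

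At stake is the value of the robustness check on one of two co-primary outcomes.

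**Working it through.** **Plan's own figures (SAP 3.3).** With two-sided alpha 0.025 and 90% power, (2.241 + 1.282)² = 12.41.

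- QoR-40: 2 × 15.5² × 12.41 / 5² = 239 per arm (240 with the t distribution); the plan states 240.
- Pain: 2 × 12.41 / 0.33² = 228 per arm. With a standardised difference of 1/3, the t-based figure is 225; the plan states 225.
- Loss: 240/0.96 = 250 and 225/0.90 = 250 per arm.

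These reproduce. The 4% and 10% losses are used below as the share of scores missing at each time.

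**Weight of one imputed score.** Trapezoid weights for 6, 24, 48 and 72 h are 9, 21, 24 and 12, which sum to 66 h. If the worst observed score is 10, discharge status changes an imputed score by 10 − 3 = 7 points. In AUC units that is 63, 147, 168 or 84 at the four times, and 7 × 66 = 462 if all four are missing. If the worst score is 8 or 9, the gap is 5 or 6 points.

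**Expected bias with no true difference.** Let m be the share of scores missing at 24, 48 and 72 h (equal in both arms) and d the discharge gap between arms. Then

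bias = m × d × 7 × (21 + 24 + 12) / 66 VAS points.

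Example: 0.10 × 0.20 × 7 × 57/66 = 0.12.

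**Null simulation.** There were 4,000 runs per scenario with 250 patients per arm, an unadjusted t test on the imputed AUC and alpha 0.025. The following are assumed, because the documents do not give them: mean pain 4, SD 2, correlation 0.6, scores missing at random at 24-72 h, and 20/50/70% of controls discharged at 24/48/72 h.

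| Missing | Discharge gap | Formula | Simulated bias (VAS) | Rejection |
|---|---|---|---|---|
| 4% | 10 points | 0.02 | −0.02 | 2.8% |
| 4% | 20 points | 0.05 | −0.05 | 3.1% |
| 10% | 10 points | 0.06 | −0.06 | 3.7% |
| 10% | 20 points | 0.12 | −0.12 | 7.8% |
| 20% | 10 points | 0.12 | −0.11 | 6.8% |
| 20% | 20 points | 0.24 | −0.23 | 23.3% |

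A negative bias favours the arm discharged sooner. With equal discharge the bias is about 0 and rejection is 2.3-2.5%. The Monte Carlo standard error near 2.5% is √(0.025 × 0.975/4000) = 0.25 percentage points, so the 4% rows are at or near simulation noise.

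**Scale.** The pain target of 0.33 SD equals 0.50-0.83 VAS points if the SD of average pain is 1.5-2.5 (assumed). A bias of 0.12 is therefore 15-24% of the target.

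**Patients without surgery.** Suppose k more of them fall in one arm of 250 and are scored 10 where an average of 4 is assumed. That arm's mean moves by k/250 × 6: 0.05, 0.12 or 0.24 points for k = 2, 5 or 10. Equal numbers in both arms would mainly add variance.

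**The case against.** The strongest reply is that nothing decisive depends on this analysis. The primary mixed model does not use the imputed values, and the rule for a positive trial (SAP 4.1) concerns the primary outcomes. That stands. A reader might infer that the trial's pain result is biased by discharge; the documents do not support it.

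Nor does earlier discharge by itself create a benefit. The score must also be missing, and the daily telephone calls are aimed at the very patients who would be scored 3.

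Discharge also carries some information about pain, since fitness requires a score of 3 or less. Giving discharged patients a lower value is reasonable in direction. What is hard to defend is a fixed gap of up to 7 points with no range around it.

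The pain outcome has other analyses: the mixed model, and the summary-measures AUC that drops patients missing the 6 or 72 hour score. They handle missing data differently, so the plan is not without comparison, and it would go too far to say that robustness cannot be tested. But neither of them specifies a departure from missing at random. Protocol 11.4 foresees multiple imputation as appropriate, and SAP 6.4 refers to SAP 6.3 for any related checks, but SAP 6.3 specifies none for pain.

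On patients without surgery, a reader might infer that the SAP scores them as in maximal pain. It does not say so. The value would be the worst observed score, not 10 by rule, and the case follows only from the silence of SAP 6.3 combined with the intention-to-treat definition. Numbers should be small, because randomisation takes place on the day of surgery where possible.

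**Conclusion.** The point holds as a weakness in a sensitivity analysis, not as a flaw in the primary result. The imputation depends on a post-randomisation event that treatment may affect. At the plan's 4-10% loss the distortion is small to moderate: 0.02-0.12 VAS points, with rejection of 2.8-7.8% against 2.5%. It becomes serious only with about 20% missing and a wide discharge gap. These figures rest on assumed discharge rates, pain distribution and missingness pattern, and on a worst observed score near 10.

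It matters because this is the only missing-not-at-random check given for co-primary pain. It is one scenario without a range, and it can favour the arm discharged sooner. That makes it a weak and potentially one-directional test, while QoR-40 has a graded one in the same section. The handling of patients without surgery needs clarifying, and affects the comparison only if their numbers differ between arms.

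**What to change.** In SAP 6.3, add a shift analysis for pain as the main missing-not-at-random check:

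- Start from the missing-at-random estimate.
- Apply a shift to the missing scores over a stated range on the 0-10 scale, for both arms together, for the intervention arm alone and for the control arm alone.
- Do not use discharge status to set the value.
- Report the shift at which the conclusion changes.

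The two existing rules need not be deleted. If kept, label them as an additional scenario.

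State also that post-operative pain is not imputed for patients who had no surgery, and report their number by arm. This departs from the definition in SAP 4.2 and should be acknowledged as such. The cost in practice is low, since a patient with no post-operative scores adds no outcome data to the mixed model either.

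The change needs SAP wording and modest programming, and no new data. The price is a range of results instead of one.

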#### 6.4 Sensitivity Analysis

For the co-primary outcomes, a sensitivity analysis will be carried out on a per-protocol basis using the definition of the PP population given in Section 4.2. This will examine the robustness of conclusions to different assumptions about departures from randomised policies. Sensitivity analyses for checking the validity of MI assumptions, if applicable, will be performed as described in Section 6.3.

The forest plots will be undertaken to compare the QoR40 among different sites.

#### 6.5 Pre-specified Subgroup Analysis

No formal subgroup analyses are planned.

#### 6.6 Supplementary/ Additional Analyses and Outcomes

No further analyses are planned.

#### 6.7 Harms

A serious adverse event (SAE) is any untoward medical occurrence that results in death, is life-threatening, requires inpatient hospitalisation or prolongation of existing hospitalisation, results in persistent or significant disability/incapacity, consists of a congenital anomaly or birth defect or is otherwise considered medically significant by the investigator.

Any adverse event (AE) occurring within 30 days of surgery will be recorded if there is a reasonable possibility it is related to either: (i) the administration of the investigational medical product (IMP) or the

control drug; or (ii) the knee replacement surgery. Expectedness and causality of AEs and SAEs will also be determined. AEs occurring more than 30 days following surgery will only be recorded if (i) the event is deemed to be serious (meets SAE criteria) and there is a reasonable possibility it is related to the knee replacement surgery; or (ii) there is a patient death.

Details of expected events related to either the administration of the IMP during surgery or the knee replacement surgery itself are provided in the trial protocol. It is noted that reported AEs related to the IMP have been shown to occur at a similar rate as those in the corresponding bupivacaine hydrochloride controls in active comparator studies.

The number of AEs occurring up to 30 days post-surgery will be reported by treatment group. The number of participants experiencing an AE will also be reported by treatment group, and the two groups will be compared. The number of SAEs, SARs, and SUSARs occurring up to 12 months post-randomisation will be reported by treatment group (Table 15). The numbers of participants experiencing an SAE, SAR or SUSAR will also be summarised by treatment group and will be compared between the liposomal bupivacaine + bupivacaine hydrochloride and bupivacaine hydrochloride alone groups by examination of the 95% confidence intervals for the difference in incidence. The analysis will be conducted for the ITT population as defined in Section 7. The number of deaths per arm will also be compared. Descriptive data on the type of AE reported, as well as MedDRA codes for the SAEs will also be presented.

**Table 15:** Summary of Serious Adverse Events (SAEs) including SARs/SUSARs

|                                                                        | Intervention | Control | Total |
|------------------------------------------------------------------------|--------------|---------|-------|
| Number of SAEs, SARs and SUSARs                                        | X            | X       | X     |
| SAEs                                                                   | X            | X       | X     |
| SARs                                                                   | X            | X       | X     |
| SUSARs                                                                 | X            | X       | X     |
| Number of participants with SAEs, SARs and SUSARs                      | X            | X       | X     |
| Average number of SAEs, SARs and SUSARs per participant (if $\geq 1$ ) | X            | X       | X     |
| Number of participants without SAE, SAR or SUSAR                       | X            | X       | X     |
| Number of deaths                                                       | X            | X       | X     |
| Number of AEs                                                          | X            | X       | X     |
| Number of participants with AEs                                        | X            | X       | X     |

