| Adverse Event (AE)                            | Any untoward medical occurrence in a participant to whom a medicinal product has been administered, including occurrences which are not necessarily caused by or related to that product.                                                                                                                                                                                                                                                                                                                                                                                                                                                                                                                                                                                                                                                                     |
| Adverse Reaction (AR)                         | 
An untoward and unintended response in a participant to an investigational medicinal product which is related to any dose administered to that participant.
 
The phrase "response to an investigational medicinal product" means that a causal relationship between a trial medication and an AE is at least a reasonable possibility, i.e. the relationship cannot be ruled out.
 
All cases judged by either the reporting medically qualified professional or the Sponsor as having a reasonable suspected causal relationship to the trial medication qualify as adverse reactions.
                                                                                                                                                                                                                                                     |

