## 525 10.2. Causality

526 The relationship of each SAE to the trial medication must be determined by a medically qualified  
 527 individual according to the following definitions:

528 **Reasonable possibility:** The adverse event follows a reasonable temporal sequence from trial medication  
 529 administration. It cannot reasonably be attributed to any other cause.

530 **No reasonable possibility:** The adverse event is probably produced by the participant's clinical state or  
 531 by other modes of therapy administered to the participant.

532 Assessment of causality (i.e. relatedness) will be recorded in the SAE form by the site PI or a delegate  
 533 (medically qualified doctor). In addition, this will be independently reviewed by a nominated clinician.

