### 534 10.2.1 Events related to IMP administration during surgery

535 Expected events related to the administration of the trial drug (EXPAREL) into surgical sites have  
 536 been determined according to the FDA approved US Prescribing Information, found in the Appendix  
 537 A of the IMPD or here: [www.dailymed.nlm.nih.gov](http://www.dailymed.nlm.nih.gov). This will be used as the Reference Safety  
 538 Information (RSI) for all safety assessments and reporting, including SUSARs.

539 Reported AEs occur at a similar rate as the corresponding bupivacaine hydrochloride controls in the  
 540 active comparator studies.

541 The surgery and the administration of the drugs are integrated components of the treatment arms.  
 542 Events may not be linked to one specific component, however, those expected events related to  
 543 knee replacement surgery are discussed in 10.2.2.

544 The most common adverse reactions (incidence greater than or equal to 10%) following EXPAREL  
 545 administration in surgical sites were nausea, constipation, and vomiting.

546 The common adverse reactions (incidence greater than or equal to 2% to less than 10%) following  
 547 EXPAREL administration were pyrexia, dizziness, edema peripheral, anemia, hypotension, pruritus,

tachycardia, headache, insomnia, anemia postoperative, muscle spasms, hemorrhagic anemia, back pain, somnolence, and procedural pain.

The less common/rare adverse reactions (incidence less than 2%) following EXPAREL administration were chills, erythema, bradycardia, anxiety, urinary retention, pain, edema, tremor, dizziness postural, paresthesia, syncope, incision site edema, procedural hypertension, procedural hypotension, procedural nausea, muscular weakness, neck pain, pruritus generalized, rash pruritic, hyperhidrosis, cold sweat, urticaria, bradycardia, palpitations, sinus bradycardia, supraventricular extrasystoles, ventricular extrasystoles, ventricular tachycardia, hypertension, pallor, anxiety, confusional state, depression, agitation, restlessness, hypoxia, laryngospasm, apnea, respiratory depression, respiratory failure, body temperature increased, blood pressure increased, blood pressure decreased, oxygen saturation decreased, urinary incontinence, vision blurred, tinnitus, drug hypersensitivity, and hypersensitivity.

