## **10.3. Procedures for Recording Adverse Events & Reporting Serious Adverse Events**

Within 30 days of the surgery, Adverse Events need to be recorded if there is a reasonable possibility they are related to the:

- Administration of the IMP or control drug
- Knee replacement surgery

These will be recorded on Adverse Event form.

If the Adverse Event is deemed to be serious (i.e. meets the SAE criteria) then this will be reported on the SAE form. Serious Adverse Events must be reported throughout the duration of the study and follow up period (12months). The sites must notify the study office in Oxford of these events within 24 hours

586 following knowledge of the event. The completed form will be sent to the Oxford study office via secure  
587 nhs.net email ([[contact]](mailto:[contact])).

588 All patient deaths, regardless of cause/relatedness, will need to be reported on the SAE form.

589 Centres will routinely monitor patient records for any events that may have been missed.

590 The study office in Oxford will perform an initial check of SAE reports, request any additional  
591 information, and ensure it is reviewed by the trial's nominated person in a timely manner and according  
592 to the relevant SOP on safety reporting. The nominated person will also perform an independent review  
593 of the causality.

594 SAEs considered related to the trial medication as judged by a medically qualified investigator or the  
595 Sponsor will be followed either until resolution, or when the *event* is considered stable.

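### The day-30 recording rule in SAP 6.7 contradicts the 12-month SAE endpoint, and protocol 10.1 and 10.2 apply three different tests of relatedness

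*Combined protocol and SAP*

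**What the plan says.** **Which events are recorded.** Up to day 30, SAP 6.7 has two limbs, the trial drug and the surgery: "Any adverse event (AE) occurring within 30 days of surgery will be recorded if there is a reasonable possibility it is related to either". After day 30 the drug limb disappears. A later event is kept only if it is serious and meets the first of these conditions, or meets the second: "there is a reasonable possibility it is related to the knee replacement surgery; or (ii) there is a patient death". The same section then plans 12-month counts: "The number of SAEs, SARs, and SUSARs occurring up to 12 months post-randomisation will be reported by treatment group (Table 15".

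Protocol 10.3 has no relatedness condition for serious events: "Serious Adverse Events must be reported throughout the duration of the study and follow". The rest of that sentence sets the period at 12 months. It also asks for every death, whatever the cause. The endpoint tables in protocol section 5 and SAP 2.2 both list SAEs to 12 months after randomisation and related AEs to 30 days after surgery.

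**When an event counts as related.**
- Protocol 10.1, adverse reaction: "a causal relationship between a trial medication and an AE is at least a reasonable possibility, i.e. the relationship cannot be ruled out".
- Protocol 10.1, serious adverse reaction: the investigator must believe, with reasonable probability, that a trial treatment was the cause.
- Protocol 10.2, for each SAE against trial medication: besides a plausible time sequence, *reasonable possibility* requires that "It cannot reasonably be attributed to any other cause". The opposite category is for events probably due to the patient's condition or to other therapy.

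Protocol 10.2.1 adds, about separating drug from surgery: "Events may not be linked to one specific component".

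**The concern.** SAEs to 12 months are a named secondary safety endpoint. If the SAP's recording rule is narrower than the protocol's, Table 15 cannot deliver the 12-month counts that the SAP promises. A reader of the results could not tell whether a late count covers all SAEs or only those tied to surgery.

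The relatedness test does a different job. It decides which SAEs become SARs, and through them which become SUSARs under protocol 10.4 and go to expedited reporting under 10.5. It also decides which SAEs are followed to resolution or stability (10.3) and which the DSMC is asked to review as related (10.6, SAP 3.4). If the same event is related under one paragraph and not under another, these counts and actions depend on which paragraph the assessor used. The product is unlicensed in the UK, so these counts matter.

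**Working it through.** No stated figure depends on these rules, so the check is a comparison of texts.

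**Step 1. Apply each recording rule to an SAE after day 30.**

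| SAE after day 30 | Protocol 10.3 | SAP 6.7 recording sentence | 12-month counts in SAP 6.7 and Table 15 |
|---|---|---|---|
| Death, any cause | reported | recorded | counted |
| Non-fatal, possibly surgery-related | reported | recorded | counted |
| Non-fatal, drug-related but not surgery-related | reported | **not recorded** | due as SAE and SAR |
| Non-fatal, related to neither | reported | **not recorded** | due as SAE |

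The third row affects SAR and SUSAR counts and the SAE total. The fourth affects the SAE total only. The SAP sentence therefore disagrees with the protocol and with the analysis planned later in its own section. A version mismatch does not explain this: SAP 1.2 names protocol V6.0 for both SAP versions.

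**Step 2. Apply each relatedness test to one SAE that could plausibly be due to drug or surgery.**

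| Test | Result |
|---|---|
| 10.1, adverse reaction | met, because the drug cannot be excluded |
| 10.1, serious adverse reaction | open; depends on how strongly the investigator believes it |
| 10.2, reasonable possibility | not met, because another cause is reasonable |
| 10.2, no reasonable possibility | met only if the other cause is the probable one |

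The phrase *reasonable possibility* thus has two incompatible meanings. An event whose other cause is plausible but not probable fits neither category in 10.2.

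**Step 3. Is such overlap expected here?** Yes. Hypotension, pruritus, nausea and vomiting appear in 10.2.1 as reactions to the trial drug. Protocol section 4 lists the same effects for opioids and says opioid side effects are seen in up to 50% of patients. This shows overlap in the kind of event; the documents do not say how often such events are serious.

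**Step 4. Size.** The documents give no rate of late SAEs and no distribution of causality judgements, so the number of events lost or relabelled cannot be computed. As scale only, with 250 patients per arm (protocol 11.2) and an assumed proportion *p* with a non-fatal SAE after day 30 in a class that the SAP sentence omits, the expected number of patients per arm is 250 × *p*:
- *p* = 0.2%: 0.5
- *p* = 0.5%: 1.25
- *p* = 1%: 2.5
- *p* = 2%: 5

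These proportions are assumptions, not figures from the plan.

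**The case against.** The best defence of the day-30 sentence is that it describes collection loosely and governs nothing. Sites work to protocol 10.3, which asks for all SAEs through follow-up and has centres check records for missed events. SAP Table 1 and the later sentences of SAP 6.7 agree with the protocol. This stands: data are lost only if someone applies the sentence in collection or analysis. It does not make the sentence correct.

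On relatedness, 10.1 lets either the reporting professional or the sponsor classify an event as a reaction, causality is reviewed independently, and the DSMC sees accruing data by arm. These are real safeguards. However, no separate test is stated for the independent review, so it may inherit the narrow one.

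A reader might infer more than the text supports:
- **That 10.2 accepts a drug cause only when no other cause is possible.** It says the event cannot *reasonably* be attributed elsewhere, which is strict but weaker.
- **That related events will be close to zero by construction.** Nothing in the documents allows that calculation.
- **That 92% of drug-related SAEs are at risk.** (365 − 30) / 365 = 92% is a share of calendar time, not of risk. The drug is one intra-operative dose, reported effective for up to 72 hours, so late drug-only SAEs may be few. Since drug and surgery are treated as integrated, many late events would still enter through the surgery limb.
- **That the narrow test in 10.2 removes non-serious AEs from the record.** Its stated scope is SAEs against trial medication. AE recording in 10.3 has its own surgery limb, and 10.2.2 has expected surgical complications documented, so many such events are still captured.
- **That unblinded investigators make the narrow test especially biased.** Any causality judgement, including the wide one in 10.1, is open to the same problem.

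**Conclusion.** Two inconsistencies in the current text hold. First, the day-30 sentence in SAP 6.7, read literally, omits all non-fatal SAEs after day 30 that are not surgery-related, against protocol 10.3, the endpoint and the SAP's own 12-month counts. The unrelated events belong to this point as much as the drug-related ones. Second, protocol 10.1 and 10.2 set three thresholds for relatedness. SAR and SUSAR counts, and the reporting and follow-up that rest on them, can be too low where the narrowest is used. Under protocol collection this second point changes labels, not the SAE total.

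Both push towards fewer events attributed to the drug, but actual undercounting is conditional: on the SAP sentence being applied over the protocol, and on assessors using 10.2 rather than the adverse-reaction wording in 10.1. The size is unknown and may be small for late drug-only events. The co-primary outcomes, the significance levels and the sample size are untouched.

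**What to change.** 1. In SAP 6.7, replace the day-30 sentence with the protocol rule: all SAEs to 12 months whatever their relatedness, and AEs possibly related to drug or surgery to 30 days. Table 15 then matches its source data.
2. Choose one relatedness test and use it in the AR and SAR definitions of protocol 10.1, both categories of 10.2, and the AE recording rule of 10.3. Changing 10.2 alone would leave the SAR wording at odds with the rest. The two categories in 10.2 should leave no gap between them.
3. Confirm which recording rule and which relatedness test sites and the independent reviewer actually used, and report this with the safety results.

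The cost is wording in two documents and a short site memo. If the narrower rules were used in practice, add some further SAE or AE forms and a causality re-review of the affected SAEs.
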